## Abstract

Introduction: The EYTO-kids (European Youth Tackling Obesity in Adolescents and Children) study aims to increase fruit and/or vegetable consumption and physical activity, decrease sedentary lifestyles, and reduce the intake of sugary drinks and fast food using an innovative methodology based on social marketing and youth involvement. Methods: This study is a pilot school-based cluster randomized controlled 10-month intervention spanning two academic years (2015–2016 and 2016–2017), with eight primary schools and three high schools randomized into and designated the control group and eight primary schools and four high schools designated the intervention group in Reus, Spain. At least 301 younger school peers per group should be included. At the intervention high schools, the adolescent creators (ACs) receive an initial 16-h training session. In total, 26–32 high school ACs (12–14 years) from the four high schools will design and implement four health-promotion activities (1 h/each) for their younger (8–10 years), primary school peers. The control group will not receive any intervention. The outcomes (fruit, vegetable, fast food and sugary drink consumption; physical activity; and sedentary behaviors) of the control and intervention groups will be measured pre- and post-intervention. Conclusion: This study describes a protocol for pilot, peer-led, social marketing and youth-involved intervention, where adolescents design and implement activities for their younger peers to promote healthy lifestyles.

## 1. Background

Unhealthy habits are associated with chronic diseases such as obesity [1]. Moreover, in developed countries, obesity is associated with socioeconomic status, and the highest rates of youth obesity are observed among low-income populations in poor neighborhoods [2]. The optimal period during which to improve healthy lifestyles is childhood or adolescence, as these habits can then continue into adulthood [3].

There are multifactorial causes for the increase in overweight and childhood obesity, but one cause is dietary: increasing hypercaloric foods with abundant fats, decreasing vegetables and fruits, etc. [4]. Another cause is the decrease in physical activity and increase in sedentary habits, such as screen time [5]. Furthermore, several studies stated that a low intake of fruit and vegetables and low physical activity contribute to an increase in excess weight in the future for young people as well as the development of metabolic diseases [6,7]. Consequently, it is necessary to reverse this situation.

To effectively prevent or reverse obesity among young people living in disadvantaged areas, it is necessary to promote healthy lifestyles, such as healthy eating and more physical activity, through a health education intervention using social marketing and peer-led methods [8].

Social marketing—defined in this context as the application of commercial marketing technologies to the analysis, planning, execution and evaluation of programs designed to influence the voluntary behavior of target audiences to encourage lifestyle choices—could help achieve broad health changes among populations by providing a framework for implementing innovative solutions to social problems and health issues (e.g., obesity) [9]. For the adequate use of social marketing, eight Social Marketing Benchmark Criteria (SMBC) have been defined [10] to achieve healthy lifestyle changes within a population [11]. A recent meta-analysis found that the inclusion of at least five SMBC, regardless of which domains are chosen for school-based interventions, could enhance efforts to prevent obesity among young people and improve the quality of the intervention [12]. 

Moreover, youth involvement is an innovative participatory strategy aimed at involving young people as active participants in certain programs [13]. This involvement affects their decisions, peers, services and communities [14]. Another strategy to encourage healthy lifestyles is peer-led education, which involves the sharing of health information, values and behaviors among same-age individuals [15]. Furthermore, when adolescents transmit health-promoting messages to younger children, which is considered to be a peer-led methodology, positive changes may be observed among the younger peers, and such messages may be more effective than messages transmitted by adults [15,16,17]. 

The European Youth Tackling Obesity (EYTO) project was a multicenter intervention that used social marketing criteria and a peer-led methodology to promote healthy lifestyles in adolescents from 4 countries: the United Kingdom, Portugal, the Czech Republic and Spain [18]. The adolescents themselves designed and implemented activities for their same-age peers. The EYTO project, specifically the Spanish intervention called “*Som la Pera*” (which means “We are cool”), was implemented in Reus, Spain. In this project, five adolescents developed 10 activities as challenges to motivate their school peers during the 2013–2014 (May 2014) to 2014–2015 (May 2015) academic years, for 12 total months of intervention. This intervention was demonstrated to be effective in promoting healthy lifestyles among adolescents, increasing fruit consumption and physical activity participation and reducing sedentary behaviours, such as screen time [19]. 

From the EYTO project experience, a further initiative has arisen: the EYTO-kids (European Youth Tackling Obesity in Adolescents and Children) project in Reus. The present project aims to improve lifestyles using peer-led mentorship conducted by adolescents in their first and second years of high school, who are designated adolescent creators (ACs), and applied to younger peers in the third and fourth grades of primary school (henceforth called younger peers). Our hypothesis is that educational intervention activities based on SMBC that were designed by ACs and conducted with younger peers living in disadvantaged neighborhoods would be effective at improving lifestyles. 

This paper describes the EYTO-kids project protocol. 

## 2. Methods/Design

### 2.1. Study Aims 

The principal aims of this study are to increase fruit and/or vegetable consumption and extracurricular physical activity, decrease sedentary lifestyles and reduce the intake of sugary drinks and fast food using an innovative methodology based on social marketing and youth involvement. The project involves the design and implementation of health-promoting activities performed by adolescents and applied to their younger school peers. 

### 2.2. Study Design and Setting

The EYTO-kids project is a school-based pilot cluster randomized controlled intervention with a duration of 2 academic years (2015–2016 and 2016–2017) that is being conducted for 10 months in Reus, Spain. In Reus, 20 public primary schools and 8 high schools that serve low-income neighborhoods were identified. Of these schools, 4 public primary schools and 1 high school decided not to participate in this project. The randomization code was computer generated with Research Randomizer software (Geoffrey C. Urbaniak and Scott Plous, Lancaster, PA, USA) [20]. Furthermore, the unit responsible for the randomization was separate from the study researchers. Because the researchers knew the names of the schools, the allocation was not blinded. Then, the primary schools and high schools were assigned to the control or intervention arm at a ratio of 1:1 via an interactive electronic response system hosted by the Nutrition and Health Technology Centre (CTNS) in Reus, Spain. The unit responsible for the randomization will take no further part in the study. Because the researchers know the names of the 4 high schools, allocation concealment is not performed. The intervention group will receive the intervention; no intervention will be performed for the control group. An evaluation will be performed before and after the intervention in both participant groups (Figure 1). 

All participants will have informed consent forms signed by their parents or guardians. The EYTO-kids project has the approval of the Ethical Committee of the Hospital Universitari Sant Joan de Reus (ref: 16-01-28/1proj1), and the trial is registered with ClinicalTrials.gov (NCT02702336). The protocol is in accordance with the Helsinki Declaration and the Good Clinical Practice guidelines of the International Conference on Harmonization (ICH GCP). This randomized trial is being conducted according to CONSORT 2010 guidelines. Furthermore, this study adheres to the following Standard Protocol Items: Recommendations for Interventional Trials (SPIRIT) (Supplementary Materials 1) and Better reporting of interventions: template for intervention description and replication (TIDier) protocol guidelines (Supplementary Materials 2).

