### 2.6. Sample Size

The sample size of this EYTO-kids project is calculated to detect a 5% rate difference among younger school peers who consume ≥1 fruit/day or practice ≥4 h/week of physical activity between the intervention and control groups. For an alpha risk of 0.05 and a beta risk of 0.1 in a bilateral comparison, 301 primary schoolchildren are required in the first group (intervention), and 301 are required in the second group (control). An estimated 30% rate loss takes into account the losses observed in the previously conducted EYTO study [19].

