## 3. Discussion

The EYTO-kids project protocol aims to promote healthy lifestyles through an innovative methodology using social marketing and peer-led youth involvement as strategies to design and implement health-promoting activities performed by adolescents for their younger school peers. 

Based on previous experience, the EYTO project uses an innovative methodology based on social marketing and a peer-led model involving adolescents who design health-promotion activities for their adolescent peers. The present study takes this concept a step further in that adolescents design health-promotion activities for their younger school peers as part of the EYTO-kids project. 

Adolescents will be able to promote healthy lifestyles and have a positive influence on their urban, low-income, younger school peers by transmitting healthy messages. 

Certain behavioral changes, such as increasing the percentage of younger school peers who consume ≥1 fruit/day and practice ≥4 h/week of physical activity, can reduce the prevalence of obesity in children. Moreover, decreasing the consumption of sugary drinks and decreasing sedentary behaviors by reducing TV hours and other screen time are tools for reducing obesity [28,29,30,31]. Childhood obesity control is complex but necessary because many risk behaviors are involved that are shaped by multiple environments and require multiple interventions involving methodological and environmental strategies [32]. 

Social marketing has been identified as a potentially effective methodological strategy to increase healthy lifestyle choices [12], and capitalizing on the value of health communication increases the likelihood that young school peers will make healthy behavioral choices [3,33,34]. 

Although the influence of older peers on the behavior of young peers at an early age has been acknowledged [13], the effectiveness of peer-led health-promotion interventions remains undetermined. Thus, to the best of our knowledge, EYTO-kids is the first project in which adolescents design and implement activities for younger primary school peers using a combination of three potentially effective methodological strategies—social marketing, peer-led interventions and youth involvement—to achieve positive behavioral changes, such as reducing obesity prevalence, which the EYTO-kids project proposes to elucidate.

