## 4. Conclusions

This study describes a protocol for pilot, peer-led, social marketing and youth-involved intervention, where adolescents design and implement activities for their younger peers to promote healthy lifestyles.

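### The trial is labelled a pilot but framed and powered as an effectiveness trial, and 8 schools per arm do not give the 90% power that section 2.6 states

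*Protocol article*

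**What the plan says.** Three places give the label. The Abstract says "This study is a pilot school-based cluster randomized controlled 10-month intervention", section 2.2 says "The EYTO-kids project is a school-based pilot cluster randomized controlled intervention with a duration of 2 academic years", and section 4 says "This study describes a protocol for pilot, peer-led, social marketing and youth-involved intervention".

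The parts that fix the purpose point the other way:
- **Hypothesis (section 1):** activities "conducted with younger peers living in disadvantaged neighborhoods would be effective at improving lifestyles".
- **Aims (section 2.1):** "The principal aims of this study are to increase fruit and/or vegetable consumption and extracurricular physical activity", with the other aims also being behaviour changes.
- **Outcomes (section 2.5):** every primary and secondary outcome is a percentage of children showing a behaviour.
- **Size (section 2.6):** a 5% rate difference, "For an alpha risk of 0.05 and a beta risk of 0.1 in a bilateral comparison", giving 301 children per group, with an estimated 30% loss.
- **Analysis (section 2.7):** generalized linear models for group differences, McNemar tests within groups, and a two-sided 5% significance level.

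Outcomes are measured in 16 primary schools, 8 per arm.

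**The concern.** A pilot and an effectiveness trial license different conclusions. The article gives the label of the first and the apparatus of the second, and never says which governs the reading of the result. A reader who takes the 90% power statement at face value would treat a non-significant result as fairly strong evidence that a 5-point benefit is absent. If real power is far lower, a non-significant result is the likely outcome even when the programme works exactly as hoped. A significant result would come from an estimate much less precise than the plan suggests.

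**Working it through.** **Inputs from the article.** Difference 5 points; two-sided alpha 0.05; beta 0.1; 301 per arm; 30% loss, not stated as before or after the 301; 8 primary schools per arm.

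**Assumptions, because the article gives neither.** Base rate p = 30–70%; ICC = 0.01–0.05, with 0 as the most favourable case.

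**1. The plan's own figure.** The usual two-proportion formula is n = [1.960·√(2p̄(1−p̄)) + 1.282·√(p₁(1−p₁) + p₂(1−p₂))]² / 0.05², with p₂ = p₁ + 0.05 and p̄ their mean. It gives 282 per arm at a base rate of 1% and 360 at 2%, so 301 corresponds to about 1.2% (or its mirror image near 94%). At 5% and 10% it gives 582 and 918. At 30%, 50% and 70% it gives 1,842, 2,095 and 1,674, all before clustering and loss. The figure 301 therefore cannot be reproduced at any base rate from 5% to 90%.

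**2. Precision with 8 schools per arm.** Children per school m = 301/8 = 37.6, or 211/8 = 26.4 if 301 × 0.7 ≈ 211 remain. Design effect DE = 1 + (m − 1)·ICC. Half-width = t(0.975; 14 df) × √(2p(1−p)·DE/n), with t = 2.145 for 16 schools.

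Example at n = 301, p = 0.5, ICC 0.05: DE = 1 + 36.6 × 0.05 = 2.83, and 2.145 × √(0.5 × 2.83/301) = 14.7 points.

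| n per arm | ICC | DE | Half-width, p = 30% or 70% | Half-width, p = 50% |
|---|---|---|---|---|
| 301 | 0 | 1.00 | 8.0 | 8.7 |
| 301 | 0.01 | 1.37 | 9.4 | 10.2 |
| 301 | 0.02 | 1.73 | 10.5 | 11.5 |
| 301 | 0.05 | 2.83 | 13.5 | 14.7 |
| 211 | 0.01 | 1.25 | 10.7 | 11.7 |
| 211 | 0.02 | 1.51 | 11.7 | 12.8 |
| 211 | 0.05 | 2.27 | 14.4 | 15.7 |

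**3. Power for a true 5-point difference.** Non-central t on 14 df, with SE = √([p(1−p) + (p+0.05)(0.95−p)]·DE/n), over p = 30%, 50% and 70%:
- 301 per arm: 16.5–19.5% at ICC 0.01, 14.1–16.4% at 0.02, 10.5–11.9% at 0.05.
- 211 per arm: 13.8–16.0%, 12.3–14.1% and 9.8–11.0%.
- 301 per arm at ICC 0: 20.9–25.0%.

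**4. What 90% power would take.** With 38 children per school, the required n from step 1 times DE = 1 + 37·ICC runs from 1,674 × 1.37 ≈ 2,294 to 2,095 × 2.85 ≈ 5,971 children per arm. That is 61 to 158 schools per arm, against 8.

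**5. Would more children per school help?** As m grows without limit, the half-width falls only to 2.145 × √(2p(1−p)·ICC/8). This is 4.9 points at p = 0.3, ICC 0.01, and 12.0 points at p = 0.5, ICC 0.05.

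**The case against.** **The reading rule is not on the page.** A reader might infer that the plan commits itself to declaring the programme effective or ineffective according to the 5% test. The documents do not support that. Section 2.7 fixes a significance level and no decision rule, and section 4 says only that a pilot protocol is described. The Discussion's statement that "the effectiveness of peer-led health-promotion interventions remains undetermined" concerns the existing literature. This stands: misreading is a risk, not a stated rule.

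**Missing pilot outputs are not an error.** A reader might also fault the article for naming no ICC or retention output. An article commonly leaves these to a full protocol or analysis plan, which is not shown. The ICC would also be weak evidence: with 16 schools of about 38 children its standard error is about 0.017 at ICC 0.02 and 0.026 at 0.05. An estimate of 0.02 would carry an interval of about 0 to 0.05 (0.02 + 1.96 × 0.017 = 0.053), too wide to size a later trial by itself. This stands too, so these outputs are optional below.

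**The power shortfall belongs to section 2.6 whatever the label.** True, and so the fix must reach 2.6. But correcting the sample-size text alone would still leave open what a 5% test in a pilot may conclude.

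**301 is a minimum, and baseline measurements may sharpen the estimate.** Both are fair. The Abstract says at least 301, and the half-widths above take no credit for baseline adjustment. Step 5 shows, however, that with 8 schools per arm extra children cannot bring the half-width much below 5 points in the best case assumed.

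**The base rate could be extreme.** Near 1%, 301 would give about 92% power before clustering. At 5% and 10% unclustered power is already down to 65% and 46%.

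**Conclusion.** The concern holds as an inconsistency with a practical consequence. The pilot label sits beside an effectiveness hypothesis, effectiveness aims, a 90% power statement and two-sided 5% tests, and the design lacks the stated power. Under the assumed base rates and ICCs, the interval extends about 9–15 points either side of the estimate with 301 per arm, or 11–16 with 211, and power is roughly 10–20%. The main conclusion does not depend on the assumed ICC: at ICC 0 the half-width is still about 8–9 points, wider than the target. It does depend on the base rate not being extreme. The finding does not extend to saying that the plan prescribes a wrong conclusion.

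**What to change.** 1. **Section 2.7.** Make the primary result the between-arm difference in each primary outcome with a 95% confidence interval that accounts for school (16 primary schools). State that, because this is a pilot, a non-significant 5% test is not evidence of ineffectiveness and a significant one is preliminary.
2. **Section 2.6.** Withdraw the 90% power statement, or restate it as the precision or power expected with 8 schools per arm under stated base-rate and ICC assumptions.
3. **Optional.** Report the school-level ICC with its 95% confidence interval, noting that it will be imprecise. Report completion of both questionnaires by arm among all consented children. The latter requires removing post-intervention completion from the inclusion criteria in section 2.3.2; as written, children without it are excluded and the proportion has no usable denominator.

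Deleting the word pilot is not an adequate alternative, since it would present an underpowered trial as definitive.

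The cost is wording and one additional model output per outcome, with no new data. The downside is a more modest permitted conclusion and a less favourable stated power.

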### 2.3. Youth Participants and Professional Experts

#### 2.3.1. ACs in High Schools

The inclusion criteria are as follows: adolescent in the first and second year of secondary mandatory high school (ESO, a Spanish abbreviation), attendance at one of the four randomized high schools designated as the intervention group, signed (by the students and their parents) informed consent, basic demographic data (name and date of birth) and completion of a lifestyle questionnaire before and after the intervention implementation. The exclusion criteria will be considered the lack of any inclusion criteria. 

The project will be offered to 26–32 ACs per high school, involving a total of 104 ACs in the intervention group. 

#### 2.3.2. Younger School Peers in Primary Schools

The inclusion criteria are as follows: younger school peers in the third and fourth grades of primary school, attendance at one of the 8 primary schools randomized in the study, an informed consent form signed by parents, basic demographic data (name and date of birth) and completion of a lifestyle questionnaire before and after the intervention implementation. The exclusion criteria will be considered the lack of any inclusion criteria. 

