### 2.5. Primary and Secondary Outcomes

The expected primary outcomes are to increase the percentage of younger school peers who consume ≥1 fruit/day and practice ≥4 h/week of physical activity. The secondary outcomes are to increase the percentage of younger school peers who consume ≥1 vegetable/day and to decrease the percentage of younger school peers who have sedentary behaviors, consume a large number of sugary drinks/day and visit fast food restaurants more than once/week. 

To evaluate the primary and secondary outcomes, younger school peers from the intervention and control groups will answer a questionnaire before and after the control and intervention group interventions composed of 4 validated questionnaires:

(a) Fruit and vegetable consumption and fast food restaurant frequency: the EnKid questionnaire [21].

(b) Physical activity practice: the AVall questionnaire [22].

(c) Sedentary behavior (time spent watching TV or/and playing videogames and using the computer): the Health Behavior in School-aged Children (HBSC) questionnaire [23].

(d) Sugary drink consumption: the HABITS questionnaire [24].

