### 2.7. Statistical Analysis Plan

The descriptive results will be expressed as the means ± standard deviation, and 95% confidence intervals will be expressed as frequency distributions.

Generalized linear models (GLMs) will be used to analyze the differences between the intervention and control groups and changes in primary and secondary outcomes before and after the intervention and control group interventions. McNemar tests will be used to analyze changes at the primary outcomes in the intervention and control groups over time in the case of dichotomous categorical variables. The main analysis will be based on the Intention-To-Treat (ITT) population, and a sensitivity analysis based on multiple imputation [25] will be conducted for all variables. One hundred datasets with no missing values will be generated using the package mice [26] for software R version 3.3.3 (The R Foundation for Statistical Computing, Vienna, Austria) [27] with the appropriate approach depending on the nature of the variable.

To allow comparability between this study and previous literature, the main analyses will also be stratified by gender.

The significance level is fixed at a bilateral level of 5%. All statistical analyses will be performed with R software version 3.3.3 and SPSS version 23.00 (SPSS, Inc., IBM, Armonk, NY, USA).

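### Eligibility requires a completed post-intervention questionnaire, so read literally the ITT population holds completers only, which contradicts the plan's own 30% loss allowance

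*Protocol article*

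**What the plan says.** Section 2.3.2 of the protocol article lists the inclusion criteria for the younger peers. Beside grade, school, parental consent and demographic data stands "completion of a lifestyle questionnaire before and after the intervention implementation". The section then adds: "The exclusion criteria will be considered the lack of any inclusion criteria". Section 2.3.1 sets the same two conditions for the adolescent creators.

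Section 2.5 makes this questionnaire the source of all primary and secondary outcomes: "younger school peers from the intervention and control groups will answer a questionnaire before and after".

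Section 2.6 expects attrition: "An estimated 30% rate loss takes into account the losses observed in the previously conducted EYTO study". Section 2.7 states: "The main analysis will be based on the Intention-To-Treat (ITT) population", and adds "a sensitivity analysis based on multiple imputation" for all variables, with 100 imputed datasets.

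Section 2.3.2 also speaks of 8 randomised primary schools. The Abstract gives eight per arm, and section 2.2 has 20 identified and 4 declining.

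**The concern.** An eligibility criterion should be something that can be known when a participant enters. Returning the second questionnaire happens after schools have been allocated and after the activities have been delivered. Because that questionnaire carries every outcome, the criterion amounts to saying that a child belongs to the study only if the child's outcome was observed.

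If the rule is followed, a child who is lost is not a participant with missing data but someone who was never eligible. The label ITT would then describe a set selected on a post-randomisation event, and the protection that randomisation gives to the comparison would no longer be assured. Allocation is not blinded and controls receive no intervention (section 2.2), so the plan offers no ground for assuming that follow-up is alike in the two arms. There is also a practical risk: baseline records of children classed as ineligible could be discarded, and then no later analysis could bring them back.

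**Working it through.** **1. The sections side by side**

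| Section | What it implies for a child with baseline data and no follow-up questionnaire |
|---|---|
| 2.3.2 | Fails an inclusion criterion, hence excluded |
| 2.6 | Belongs to an anticipated 30% loss, hence in the study and then lost |
| 2.7, ITT | Should be counted in the arm of the child's school |
| 2.7, imputation | A natural candidate for imputation |

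The first row cannot stand with the other three. No section defines ITT in a way that overrides the eligibility rule.

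**2. The plan's own sample size**

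Section 2.6 gives 301 per group for a 5-point difference, two-sided alpha 0.05 and beta 0.1. No base rate is stated, so 301 cannot be reproduced from the document's inputs. That is a separate matter. Here only the 301 and the 30% are needed. The text does not say whether 301 is before or after the loss, so both readings are shown.

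**3. How many children the criterion rules out**

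- If 301 is the number enrolled: completers = 301 × 0.70 = 210.7, about 211. Ruled out = 301 × 0.30 = 90.3, about 90 per arm and about 180 in total.
- If 301 is the number of completers: enrolled = 301 / 0.70 = 430. Ruled out = 430 − 301 = 129 per arm and 258 in total.

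**4. What this could do to the estimate (assumptions, not figures from the documents)**

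Let r be the fraction retained in an arm, c the prevalence among completers, and c − g the prevalence among dropouts. The prevalence among all children in the arm is

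p = r·c + (1 − r)(c − g) = c − (1 − r)·g,

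so completers overstate it by (1 − r)·g. With subscripts I for intervention and C for control, the bias in the difference is

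(1 − r_I)·g_I − (1 − r_C)·g_C.

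| r_I | r_C | g_I (points) | g_C (points) | Bias (points) |
|---|---|---|---|---|
| 0.70 | 0.70 | 10 | 10 | 3 − 3 = 0 |
| 0.70 | 0.70 | 10 | 0 | 3 − 0 = +3 |
| 0.70 | 0.70 | 20 | 0 | 6 − 0 = +6 |
| 0.70 | 0.70 | 0 | 10 | 0 − 3 = −3 |
| 0.65 | 0.75 | 10 | 10 | 3.5 − 2.5 = +1 |

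The target difference in section 2.6 is 5 points. Either sign is possible, and so is zero.

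**5. School count**

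Section 2.2: 20 − 4 = 16 participating primary schools. Abstract: 8 + 8 = 16. Section 2.3.2: 8.

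**The case against.** The strongest reply is that the clause is a loosely worded participation requirement. A 30% loss allowance, an ITT main analysis and 100 imputed datasets make most sense if children without follow-up are kept. Section 2.4.1 has teachers choose the adolescent creators under the same inclusion criteria before training starts, when no follow-up questionnaire could be checked. This is a fair reading of what was meant. It is a reason to correct the clause, but it does not remove the conflict, because the text as it stands still says the opposite.

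Several stronger inferences are tempting and should not be drawn:

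- *That imputation would have nothing to do.* A returned questionnaire can have unanswered items. What the criterion takes away is the wholly missing follow-up.
- *That the main model would drop children without an outcome in any case.* Section 2.7 names generalized linear models without giving their structure, and does not say that the analysis is complete-case. A repeated-measures form could retain children who have only baseline data. Such detail may sit in an analysis plan that is not shown.
- *That the imputed analysis must become the main one.* This is a debatable choice. If missingness depends only on modelled baseline covariates, a covariate-adjusted complete-case model can be as valid; if it depends on the unobserved outcome, standard imputation does not repair it.
- *That completion depends on engagement with the programme.* No section says so.
- *That control schools are ineligible.* Section 2.3.2 does not say which 8 schools it means, and section 2.5 has both groups answering the questionnaire.

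**Conclusion.** The point stands as a contradiction in the text. Applied as written, section 2.3.2 conditions the study population on a post-randomisation event that supplies every outcome, and this cannot be squared with the loss allowance in section 2.6 or the ITT analysis with imputation in section 2.7. At the plan's own 30% it concerns about 90 of 301 children per arm, or about 129 of 430, depending on what 301 denotes.

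A reader might infer that the trial's estimate will be biased by about 3 points, more than half of the 5-point target. The documents do not support that. The figure needs an assumed 10-point gap between completers and dropouts in the intervention arm and none in the control arm; under equal loss and an equal relation to outcome the bias is zero, and under the reverse assumption it is −3. Neither direction nor size can be derived from the plan. The conclusion rests on the conflict between the sections, not on any of these scenarios.

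**What to change.** 1. In sections 2.3.1 and 2.3.2, delete the words *and after*, so that eligibility rests on conditions known at baseline. Treat the post-intervention questionnaire as an outcome assessment.
2. Keep the baseline records of all children lost to follow-up.
3. In section 2.7, define the ITT population as all consented third- and fourth-grade children with a baseline questionnaire in the randomised primary schools, analysed in the arm to which their school was allocated.
4. State that the multiple imputation already planned covers children with no follow-up questionnaire as well as unanswered items.
5. Reconcile the 8 randomised primary schools in section 2.3.2 with the 16 (8 per arm) that follow from the Abstract and section 2.2.

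The cost is a few changes of wording. No new data or visits are needed, provided the baseline records of lost children have not been discarded.
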